##### System level

3.6.2.3

To evaluate impact of *Connect Local* on health services use such as hospitalisations, General Practitioner (GP) visits and other health service visits, several health service-related indicators will be collected from participants in both the intervention and comparator groups at baseline, 3, 6 and 12 months using the Resource Use Questionnaire [adapted from Fletcher (65)], as per Tables 2, 3. Using interviews, the service provider morale in general practice and other referral agencies and healthcare provider satisfaction will also be gathered at three months from when their patients engaged in the *Connect Local* program.

###### Sample size calculation

3.6.2.3.1

The primary outcome is a reduction in loneliness at 3 months for participants receiving the *Connect Local* program, when compared to the comparator group. A program conducting similar activities found a statistically significant reduction in mean UCLA-3 scores of 0.85, with a medium effect size of 0.37 (73). Using this effect size at 0.05 alpha, 76 participants are required in the intervention group to reach 0.9 power. Allowing for 15% attrition at the 3 month follow up, we have increased the sample size to 88. A matched comparator group will be recruited at a 1:1 ratio, as such a total of 176 participants will be recruited to the intervention and comparator groups.

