##### Establishing impact

3.6.3.2

This stage will determine those aspects of change that would have happened anyway or are a result of other factors. Such aspects will be eliminated from consideration. Qualitative and quantitative data (surveys on loneliness, social connection, depressive symptoms, wellbeing and quality of life at baseline, 3, 6 and 12 months) will provide this evidence. Monetised outcomes will be discounted on the basis of what would have happened without the intervention (deadweight), what outcomes are displaced by the intervention (displacement), who else has contributed to the outcomes aside from the funder (attribution), and whether experience of the outcomes declines over time (drop off).

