For quantitative, binary or dichotomous individual level outcomes (scales that have cut-off scores: loneliness (UCLA-3), social anxiety, depressive symptoms) additional analysis will be undertaken addressing the research question: do the interventions differ in their effectiveness, such that individuals in the intervention group experience a greater improvement in their probability of achieving the desired outcome compared to those receiving usual care. Generalised linear mixed models (GLMMs) for dichotomous outcomes will be used as well as GEE. The typology of missing data will be investigated to make sure that the assumptions of the adopted statistical technique are not violated. Our choice of GLMMs is based on the specific characteristics of the data, as well as the advantages provided by GLMMs in handling dependent responses in longitudinal or repeated measures studies. As highlighted in Breslow and Clayton (75), GLMMs incorporate random effects into the linear predictors and are particularly well-suited for modelling the dependence among response variables in such study designs.

Selection of the model that best fits the data will be based on the low goodness-of-fit measures such as the Akaike information criterion (AIC) and Bayesian information criterion (BIC). Additionally, the log-likelihood ratio test will be employed as another method for evaluating model fit.

All quantitative community and system level variables, as well as the goal attainment will be analysed descriptively. Descriptive statistics will be presented as proportions, means (standard deviations) or, for variables that did not conform to a normal or log-normal distribution, medians (interquartile range).

Statistical analysis will be performed using STATA V.15.0 (STATA Corp LP., College Station, Texas, United States). We will use a Type I error rate of 5% to indicate statistical significance, with 95% confidence intervals (CI).

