**BOX 1 Tools used to calculate Social Return on Investment (SROI)**

**Tools of SROI**
Establishing impact (attribution, deadweight, displacement, drop-off):To minimise the risk of overclaiming the benefits it was necessary to account for deadweight, displacement, attribution, and attrition.*Deadweight:* responds to the question: ‘How much of the outcome would still be attained without the activity delivered?’We will use the quantitative data captured in the comparator group to ascertain this information, measured as a percentage, and then that percentage of the outcome will be deducted from the total quantity of the outcome.*Displacement* responds to the question: ‘Were there any activities with the same outcome displaced by the intervention being evaluated?’We will capture this information when collecting service information from participants involved in the program and comparing them to what was captured in the comparator group – using a percentage and deducted from the total outcomes.*Attribution* responds to the question; ‘Who else contributed to the attainment of the outcome?The research team will identify all relevant stakeholders and to assess how much of each outcome could be attributed to the delivery of Connecting Communities to Care with due circumspection. This will be calculated as a percentage.*Drop-off* responds to the question: ‘How much of the outcome is lost in the years post intervention?’To calculate the percentage of the outcome lost in the years after delivery of the intervention. It is calculated by deducting a fixed percentage from the remaining level of outcome at the end of each year. This will be calculated as a percentage.

*Calculating the SROI:*

The calculation of the SROI will consider the total value of the inputs in the program. The discounted, monetised value of benefits and outcomes will be divided by total investment (inputs) to estimate the SROI ratio.

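### The 0.9 power claim is not supported for the planned group contrast: 76 fits a one-group or paired calculation on one program's reported reduction, with no allowance for comparator change or comparator sampling error

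*Protocol article*

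**What the plan says.** Section 3.6.2.3.1 (Sample size calculation) sets the target: "The primary outcome is a reduction in loneliness at 3 months for participants receiving the *Connect Local* program, when compared to the comparator group". Section 3.6.2.1 likewise describes mean change from baseline against the comparator, and section 3.7.1.1 plans linear mixed models with group, time and their interaction. The quantity tested is therefore a between-group difference in change.

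The effect is taken from outside, from a similar program that "found a statistically significant reduction in mean UCLA-3 scores of 0.85, with a medium effect size of 0.37". No control group in that source is mentioned. The number follows directly: "Using this effect size at 0.05 alpha, 76 participants are required in the intervention group to reach 0.9 power". Attrition is then added: "Allowing for 15% attrition at the 3 month follow up, we have increased the sample size to 88". A comparator group matched 1:1 brings the total to 176.

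The section does not state sidedness. Section 3.7.1.1 says "We will use a Type I error rate of 5% to indicate statistical significance, with 95% confidence intervals (CI", which points to a two-sided 5% test.

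The economic sections treat change without the program as something to be measured. Section 3.6.3.2 says "This stage will determine those aspects of change that would have happened anyway or are a result of other factors". Box 1 defines deadweight by asking "How much of the outcome would still be attained without the activity delivered" and takes the answer from the comparator group. No expected size is given.

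**The concern.** A between-group trial has to be sized on the net difference between groups, with the sampling error of both groups in the formula. The figure used here reads as one program's own fall in score, and it enters a calculation that appears to involve only the intervention group. If so, two things are left out:

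- **Comparator change.** Any fall in the comparator's UCLA-3 scores is subtracted from the effect. The calculation implicitly sets that fall to zero.
- **Comparator sampling error.** A difference between two independent means has twice the variance of one mean at the same group size and SD. A flat comparator is therefore necessary for the stated power but not sufficient.

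At stake is how the result is read. The Discussion and Conclusion present the trial as a source of robust evidence for decision makers. A non-significant result set against a claimed power of 0.9 would look like stronger evidence against the program than the design can give.

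**Working it through.** **Inputs.** From section 3.6.2.3.1: effect 0.85 points, standardised effect d = 0.37, alpha 0.05, power 0.90, n = 76, 15% attrition, 88 per group. Assumed: a two-sided test, from the 5% error rate with 95% intervals in section 3.7.1.1. Derived: SD = 0.85/0.37 = 2.30, taken to apply to the measure that is analysed.

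**1. Reproducing the 76.** With z values 1.960 and 1.282 (sum 3.2415):

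- One-sample or paired: n = (3.2415/0.37)² = 76.75. This is within one of the stated 76. At n = 76 the normal-approximation power is 0.897. The t-based requirement is about 79.
- Two independent groups: n per group = 2 × (3.2415/0.37)² = 153.5, so 154. This does not reproduce 76.
- Other readings also fail: two-group, one-sided, 90% power gives 126; one-sample, one-sided gives 63; two-group at 80% power gives 115 (two-sided) or 91 (one-sided).

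Of the forms tried, only the two-sided one-sample or paired calculation comes close to 76.

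**2. Retained numbers.** 76 × 1.15 = 87.4, giving the stated 88. A 15% loss from 88 leaves 88 × 0.85 = 74.8, about 75 per group.

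**3. Two-group power with a flat comparator.** With 75 per group, d × √(75/2) = 0.37 × 6.124 = 2.266. Subtracting 1.960 gives 0.306, and the normal probability is 0.62. The two-sample t calculation gives 0.61. This is the effect of the comparator's sampling error alone.

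**4. Sensitivity to comparator change.** The protocol gives no expected comparator change, so the fractions below are assumptions. Net effect = 0.85 × (1 − fraction), and d = 0.37 × (1 − fraction). Two-sample t power, 75 per group:

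| Share of 0.85 occurring without the program | Net points | d | Power |
|---|---|---|---|
| 0% | 0.85 | 0.370 | 61% |
| 20% | 0.68 | 0.296 | 44% |
| 40% | 0.51 | 0.222 | 27% |
| 50% | 0.425 | 0.185 | 20% |

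On the one-sample or paired formula itself with n = 76, the normal-approximation power falls from 0.90 to 0.73 at 20% and 0.36 at 50%. The comparator-change issue therefore remains even if the form of the calculation is accepted.

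**5. Detectable difference.** With 75 per group and 90% power, the t-based d is 0.533, and 0.533 × 2.297 = 1.22 points.

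**6. Possible gain from baseline adjustment.** If 2.30 is the SD of scores, adjusting for baseline with correlation r multiplies the SD by √(1 − r²). With a flat comparator and 75 per group, power is about 74% at r = 0.5 and 88% at r = 0.7. If 2.30 is already the SD of change, this full gain would not apply. The protocol does not say which SD it is and claims no such gain.

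**The case against.** **The source's design is unseen.** The protocol does not say that the cited program was uncontrolled, and a sample-size formula cannot reveal how a cited study was run. This stands: that 0.85 is a within-program change is an inference from the wording, and the near match to a one-group formula is consistent with it without proving it.

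**A paired reading is possible.** The comparator is matched 1:1, and the same formula fits pair differences with a standardised effect of 0.37. On that reading the effect would already be net of the comparator. But section 3.5.2 describes recruitment monitored in blocks of five by age and gender, and section 3.7.1.1 plans no analysis of matched pairs. The reading has little support.

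**The economic sections do not contradict the sample size.** A reader might infer that section 3.6.3.2 and Box 1 say the opposite of the power calculation. They do not. They describe a standard step that measures what would have happened anyway, and the answer could be zero. They show only that the protocol allows for such change.

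**Regression to the mean is tempered.** Screening for loneliness, isolation or depressive symptoms might suggest that both groups will improve by selection alone. But Table 3 repeats UCLA-3 at baseline after screening, the outcome is change from baseline, and entry is possible on any of the three criteria. Some regression may remain; its size cannot be read from the protocol.

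**The power range is assumed.** The 44%, 27% and 20% figures rest on fractions chosen for illustration. A comparator that worsens would enlarge the net effect. This also stands.

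**Conclusion.** The stated 0.9 power is not supported for the planned group-by-time contrast. The calculation matches a one-sample or paired form, and as written it allows for neither comparator change nor comparator sampling error. With 75 retained per group, two-sided 5% and SD 2.30, power is about 61% with a flat comparator, and 90% power exists only for a net difference of about 1.22 points. The figures of 44% to 20% for a comparator that accounts for 20% to 50% of the 0.85 are a sensitivity range on assumed values.

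A reader might go further and conclude that the target effect is proven too large. The protocol does not support that: it does not state the source's design, gives no expected comparator change, and leaves open whether 2.30 is an SD of scores or of change. Baseline adjustment could recover part of the lost power (about 74% at a correlation of 0.5 and 88% at 0.7, flat comparator), but these correlations are assumptions too. Even at 0.7 with no comparator change, power stays slightly below 0.9.

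**What to change.** Keep 88 per group and rewrite the sample size paragraph:

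- State whether 0.85/0.37 is a within-program change or is net of a control, and whether the implied SD of 2.30 is of scores or of change.
- Replace the 0.9 power claim with two-group power for the planned contrast at 3 months. Give it over a stated range of comparator change that includes zero (for example 0% to 50% of 0.85), with the assumed SD and baseline correlation.
- Add the smallest net difference detectable at 90% power with 75 per group: about 0.53 SD, or 1.22 points, without baseline adjustment.

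If the source effect proves to be net of a control, saying so settles the comparator-change part; the two-group formula is still needed. The cost is wording only, with no extra participants. The downside is that the stated power becomes less favourable.

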##### Individual level

3.6.2.1

This is the level at which individuals are impacted directly, including older community members, volunteers and health and social service providers.

For older community members, we will consider the primary outcome as a mean change in loneliness, from baseline at 3, 6 and 12 months for participants receiving the *Connect Local* program, when compared to the comparator group. This will be measured using UCLA-3 as informed by previous research that support the sample size calculations (58). At this stage, there is insufficient research data to calculate sample size when using UCLA-4 (57), however this tool has been recommended for use by community organisations by Australia’s national network, Ending Loneliness Together (71), therefore we will also utilise this tool to capture loneliness to ascertain whether it can be utilised with this cohort in future studies.

As outlined in Tables 2, 3, secondary outcomes, including social isolation, social anxiety, depressive symptoms, and improvement in quality of life and wellbeing, are a mean change from baseline at 3, 6 and 12 months for participants receiving the *Connect Local* program, when compared to the comparator. Achieved goals, as measured by the Goal Attainment scale (64), will also be gathered from the intervention group.

For community volunteers involved in the *Connect Local* program, as per Tables 2, 3, we will collect health-related quality of life and wellbeing measures at baseline, 3, 6 and 12 months.

Perceptions of the program will be collected from community members in the intervention group, volunteers and service providers involved in referred to the *Connect Local* program through interviews or focus groups at three months from participant baseline. Questions will invite participants to share their thoughts around the following aspects of the program: Relational (trust and trustworthiness, obligations and expectations, identity and identification), Cognitive (shared language, codes and narratives; shared values, attitudes and beliefs; and shared goals and purpose), and Structural (roles, rules, precedents and procedures).

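### The stated 90% power is not supported for the intervention-versus-comparator comparison: 76 matches a one-group formula, and a plain two-group test at the planned size has about 61%

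*Protocol article*

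**What the plan says.** Section 3.6.2.3.1 (Sample size calculation) opens with "The primary outcome is a reduction in loneliness at 3 months for participants receiving the" program, and completes the sentence by setting that reduction against the comparator group. Section 3.6.2.1 (Individual level) has the same contrast over more time points: "we will consider the primary outcome as a mean change in loneliness, from baseline at 3, 6 and 12 months", again relative to the comparator. The analysis in 3.7.1.1 (Quantitative data analysis) is a linear mixed model with group, time and their interaction. All three places describe a between-group comparison.

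The planning effect comes from a similar program that "found a statistically significant reduction in mean UCLA-3 scores of 0.85, with a medium effect size of 0.37". The article mentions no control group for that result and does not say which SD the 0.37 uses. From it follows: "Using this effect size at 0.05 alpha, 76 participants are required in the intervention group to reach 0.9 power". Attrition comes next: "Allowing for 15% attrition at the 3 month follow up, we have increased the sample size to 88". Only then is a matched comparator added 1:1, for a total of 176.

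**The concern.** The number required is derived for the intervention group alone, from what reads as a before-after reduction, and the comparator is attached afterwards with no change to the number. A difference between two independent means has twice the variance of a single mean change at the same n per group and the same SD. A number that gives 90% power for a one-group change therefore gives much less for the difference between groups.

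The stated power tells readers how to weigh a result that is not significant. If it belongs to a different comparison from the one tested, such a result would be set against a sensitivity that the design has not been shown to have.

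**Working it through.** **Inputs.** From 3.6.2.3.1: standardised effect d = 0.37, alpha 0.05, power 0.90, 15% attrition at 3 months, 88 per group, 1:1. That section does not state sidedness. Two-sided is assumed, because 3.7.1.1 pairs a 5% Type I error rate with 95% confidence intervals.

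**1. Reproducing 76.** The one-sample (paired) formula with the normal approximation is

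n = (1.960 + 1.2816)² / 0.37² = 10.507 / 0.1369 = 76.75.

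This gives 76 if truncated and 77 if rounded up. The exact paired t test gives 79.

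**2. The two-group comparison at the same inputs.**

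n per group = 2 × 10.507 / 0.1369 = 153.5, so 154; the t test gives 155.

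A one-sided test still needs 126 per group. At 80% power the two-sided normal figure is 115 per group and the one-sided figure 91. None of these gives 76.

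**3. Attrition.** 76 × 1.15 = 87.4, which rounds up to the stated 88. But 88 × 0.85 = 74.8, so about 75 per group are expected at 3 months, slightly fewer than 76.

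**4. Power at the planned size.** Two-sided two-group t test, d = 0.37 taken as the between-group difference in SDs of the analysed variable:

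| n per group | Power |
|---|---|
| 75 (88 less 15%) | 0.615 |
| 76 | 0.620 |
| 88 (no loss) | 0.685 |

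A one-sided test with 75 per group has 0.73.

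**5. If 0.37 is on the raw-score SD.** Let r be the correlation between baseline and 3 months. The article gives no value, so r is an assumption here. The effective standardised difference is 0.37/√(2(1−r)) for change scores and 0.37/√(1−r²) with baseline adjustment. With 75 per group:

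| Assumed r | Change scores: effect, power | Baseline-adjusted: effect, power |
|---|---|---|
| 0.4 | 0.338, 0.54 | 0.404, 0.69 |
| 0.5 | 0.370, 0.61 | 0.427, 0.74 |
| 0.6 | 0.414, 0.71 | 0.462, 0.80 |
| 0.7 | 0.478, 0.83 | 0.518, 0.88 |

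Power reaches 0.90 at r of about 0.76 for change scores and about 0.72 with baseline adjustment.

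**6. Detectable difference with 75 per group.** Solving the same t-test power function for d gives 0.46 SD at 80% power and 0.53 SD at 90%, against the planned 0.37.

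**The case against.** **The longitudinal model may recover the power.** This is the best defence, and part of it stands. If 0.37 is on the raw-score SD and repeated scores are strongly correlated, the planned model could come near 90%. The source of the 0.37 is not available here, so that cannot be ruled out. A reader might infer that the design simply has 61% power. The documents do not support that as a fixed property: it holds for a plain two-group test with 0.37 on the analysed scale. Equally, the article states no correlation, so it does not support 90% either.

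**The groups are matched.** A matched-pair test with a within-pair outcome correlation of 0.5 has a pair-difference SD of √(2(1−0.5)) = 1 in raw-SD units, so it also gives 76.75, here as a number of pairs. This shows that the formula alone cannot settle where the 76 came from. A reader might infer that a before-after calculation is proven. It is not, although the wording (a number for the intervention group, with the comparator added later) points strongly that way. As a justification for 90% the defence is weak: 3.5.2 matches on age and gender only, monitored in blocks of five, no pair correlation is stated, and the mean structure in 3.7.1.1 has no pair term.

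**The detail belongs in the full protocol or SAP.** An unstated correlation alone would be no finding. The article, however, states a power figure together with its inputs, and those inputs do not yield that figure for the comparison named in the same paragraph.

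**The attrition slip is trivial.** Agreed. It is about one person per group and moves power from 0.620 to 0.615.

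**Conclusion.** The stated 90% power is unsupported for the primary between-group comparison. From the article's own inputs, 76 fits a one-group formula, and a two-group t test needs about 155 per group. At the planned size, with about 75 per group at 3 months, a plain two-sided test has about 61% power at a between-group difference of 0.37 SD on the analysed scale, so the chance of missing that effect is nearly 4 in 10. Under the raw-score reading, power runs from 0.54 to 0.88 over assumed correlations of 0.4 to 0.7, depending on the analysis.

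The conclusion that 90% is unsupported does not depend on which value in that range is right, or on how the 76 was obtained. The size of the shortfall does depend on the SD behind 0.37 and on the correlation, and neither is stated. Nor do the figures show that the trial must enrol 155 per group, which a reader might infer: that number rests on the same plain-test assumption. What is wrong is the stated power, and it can be corrected at the planned size.

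**What to change.** In 3.6.2.3.1:

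- Withdraw the 90% power claim for the intervention-versus-comparator comparison.
- State which comparison the 76 was calculated for, and which SD the 0.37 refers to (raw score or change score).
- Restate power for the planned size as about 61% under a plain two-sided two-group test with 75 per group. Give the range under assumed baseline-follow-up correlations alongside it, labelled as an assumption.
- Give the detectable differences with 75 per group: 0.46 SD at 80% power and 0.53 SD at 90%.
- State that 88 recruits with 15% loss leave about 75 per group, not 76.

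This rewords one paragraph. It needs no extra participants and no change to the analysis. The cost is a less favourable stated power.
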